### Data collection and management

Outcome data for the ACT trial will be collected through the existing MNH registry in the GN sites. This registry includes all the outcome variables including data to 42 days postpartum. Forms specific for ACT were developed to collect process outcomes.

A weekly data transmission from the research units to the Data Center will be completed using the system and transmission procedures currently in place for GN studies at each site. The data entry software will be programmed to conduct range checks and simple consistency checks of the data. Double data entry verification will be used to check for ID and data errors. An error rate of less than 0.3% is considered acceptable.

The Data Management System is password protected. It will require a user ID and password to be entered to ensure that only trained, authorized personnel have access to the data.

### Data analysis

The primary analysis will compare post-intervention outcomes between intervention and control clusters, controlling for country, using two complementary approaches. First, a cluster-based permutation test that is appropriate for the stratified randomization process be used to develop a formal hypothesis test and interval estimates of the treatment difference between the two arms. A model-based analysis will be used to assess whether the inferences generated by the permutation test are robust enough to control for potential confounders and to describe any evidence of differential treatment effects in the different countries. Although this study is not powered to evaluate treatment by country interactions formally, any evidence of such interactions will be described through the model-based analysis of this primary outcome.

An intent-to-treat analytic approach will be used for both the permutation test and for the model-based analyses, in that any cluster assigned to the intervention will be considered treated, whether or not the ACT intervention was delivered in that cluster. Also, both analyses will use country as a blocking or stratification variable in the analysis to reflect the randomization scheme.

To facilitate the model-based primary analysis, a detailed analysis of baseline variables of the two groups (intervention and control clusters) will be performed to assess the extent, if any, of baseline imbalances between the two groups of clusters. If baseline differences between the treatment arms are identified, the covariables representing the imbalanced variables will be used for adjusted analyses. Imbalances at the cluster level (e.g., proportion of hospital births, type of birth attendant) can be adjusted in the model-based analysis. Because the primary interest is in the decrease in the marginal neonatal mortality rate at the cluster level, the generalized estimating equations (GEE) method of Liang and Zeger
[21] as implemented through the SAS procedure GENMOD will be used for the primary analysis. The model will control for cluster-level effects by assuming country-specific correlation within clusters, and all inferences will be based on the empirical correlation matrix proposed by Liang and Zeger
[21]. Additional details of the model will be specified in the Statistical Analysis Plan.

In addition to the permutation tests and GEE models described above, which focus on marginal risk in the population, we will evaluate the effect of the outcome on subject level risk by modeling the binary outcome using generalized linear mixed models as implemented through the SAS procedure GLIMMIX. In this procedure, cluster will be treated as a random effect, with the cluster-specific risk nested within intervention assumed to have a Gaussian distribution. Again, both the GEE model and the generalized linear mixed model will examine the effects of potential confounders on mortality risk and the heterogeneity of treatment effects across country.

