### Participating clusters

The Global Network for Women’s and Children’s Health Research (GN) is comprised of seven geographical study sites, located in low- and middle-income countries, which function as research units for the various maternal and neonatal studies implemented by the network. Each site has research clusters, with 6 clusters in Argentina, 10 clusters in Zambia, 10 clusters in Guatemala, 20 clusters in Belgaum, India, 20 clusters in Nagpur, India, 20 clusters in Pakistan and 16 clusters in Kenya. Seven GN sites will participate in the ACT study and 102 clusters will be available for the implementation of this protocol. The sizes of the clusters differ across and within the GN sites, but each cluster was selected because it had 300 to 500 deliveries per year per cluster. The GN clusters include both rural and urban settings, with deliveries taking place at home and in health facilities. At this time, 40% of deliveries in the participating clusters occur in home or clinic settings with TBAs.

This is an intent-to-treat design and thus all pregnancy outcomes of women who deliver in the study clusters and provide consent will be collected. Cluster-level inclusion criteria include GN clusters with at least 250 deliveries per year that consent to participate. Participant-level inclusion criteria include all pregnant women living in and delivering in the study cluster, and identified as having high risk for preterm birth who are eligible to receive intramuscular corticosteroids and, in settings where it is not the standard of care, provide consent.

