### Randomization procedures

Data from the Maternal and Neonatal Health Registry (MNH) - a prospective, population-based study of pregnancy outcomes at the seven GN sites - will be used as a baseline to select the clusters and to ensure that the underlying neonatal mortality rates are reasonably balanced across arms through the randomization procedure
[16]. The 102 clusters will be allocated to the control or intervention groups. Because the GN sites differ substantially, simple random allocation may not provide adequate balance in the groups
[17]. To address this problem, we will implement a stratified randomization procedure with strata defined based on GN site, participation arm in a previous GN trial, the Emergency Obstetric and Neonatal Care trial
[18], and neonatal mortality rate. The number and size of the clusters, as well as the balanced randomization procedure will make a clinically important imbalance in relevant prognostic factors unlikely.

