GN sites have different mean birth weights; those from Asian sites are much lower than those from African and Latin American sites. Using the same birth weight (e.g., < 2500 g) as a cutoff point at all sites would include a higher proportion of Asian babies, whose mean birth weights are ~2700 g, and most of them would be SGA babies rather than preterm. To avoid this, we will use different cutoff points for each country to select the 10% smallest babies in each GN site. Using data from the MNH study for each GN site, we set a birth weight cutoff point, rounded to 100 g, that would select the smallest 10% of infants as a proxy for preterm births (< 36 weeks GA). Using this rule, the cutoff point for sites in Argentina, Zambia, and Kenya was 2500 g; for sites in Guatemala and Karnataka, India, was 2400 g; and for sites in Nagpur, India, and Pakistan was 2200 g. The overall prevalence of LBW for all sites according to those weight limits is 8.2%, with an 11.4% neonatal mortality at 7 days. A birth weight of 750 g will be used as a cutoff point for the lower birth weight limit for analysis purposes, except for those GN sites where babies with birth weights < 1000 g are considered abortions.

The primary and secondary outcomes in LBW babies, the outcomes in all infants and their mothers, and the process outcomes (to be measured only in the intervention clusters) are shown in Table
1. LBW babies are defined as newborns with birthweight below the 10^th^ percentile of the site.

**Table 1 T1:** Study outcomes

**Outcome measures in infants with birth weight below 10**^**th**^**percentile and their mothers**	**PRIMARY**
	- Neonatal mortality at 28 days

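### Country is named as the blocking variable that reflects the randomisation, but clusters are randomised within site, earlier-trial arm and mortality strata; the cost is consistency and possibly power, not validity

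*Protocol article*

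**What the plan says.** Randomization procedures: allocation is stratified, with "strata defined based on GN site, participation arm in a previous GN trial, the Emergency Obstetric and Neonatal Care trial", and, as a third factor, neonatal mortality rate. The reason given is that the sites differ substantially.

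Data analysis: the primary comparison controls for country. It has two parts, "a cluster-based permutation test that is appropriate for the stratified randomization process", which supplies the formal test and the interval estimates, and a model-based analysis. The section then states that "both analyses will use country as a blocking or stratification variable in the analysis to reflect the randomization scheme". Further covariates enter the model conditionally: "If baseline differences between the treatment arms are identified, the covariables representing the imbalanced variables will be used for adjusted analyses". Additional model details are left to the statistical analysis plan.

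Participating clusters lists seven sites in six countries, including "20 clusters in Belgaum, India, 20 clusters in Nagpur, India, 20 clusters in Pakistan". Outcome measures sets the birth-weight cut-off at 2400 g for the Karnataka site, while the cut-off "for sites in Nagpur, India, and Pakistan was 2200 g". As Nagpur is named separately, the Karnataka site must be Belgaum.

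**The concern.** A permutation test is exact when its reference allocations are drawn in the same way as the actual one. If allocation is balanced within fine strata but the test permutes within coarser blocks, the reference set includes allocations that the design excludes. Variation that the design removed returns to the reference distribution. The test then rejects too rarely, and intervals obtained from it are too wide. How much power this costs depends on how strongly the strata predict the outcome.

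The conditional covariate rule does not repair this for the models. Stratification factors are balanced by design, so a rule that adds only imbalanced variables will tend to leave them out.

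**Working it through.** **1. The two schemes side by side**

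| Factor | In the randomisation | In the stated blocking |
|---|---|---|
| GN site | yes, 7 sites | only as country, 6 levels |
| Earlier-trial arm | yes | no |
| Baseline neonatal mortality | yes | no |

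Clusters: 6 + 10 + 10 + 20 + 20 + 20 + 16 = 102. Country merges Belgaum and Nagpur: 20 + 20 = 40 clusters, with different weight cut-offs.

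**2. What permuting within country would admit**

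A split of 14/6 in Belgaum and 6/14 in Nagpur is 20/20 for India, so it would be in the reference set. If allocation is 1:1 within strata, each stratum with an odd number of clusters adds at most 1 to a site's imbalance. A 14/6 split has an imbalance of 8, so it needs at least eight odd strata in that site. With two earlier-trial arms and two mortality levels (assumed; the number of levels is not given) a site has only four strata.

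**3. The plan's own power figure**

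Inputs from Sample size: 90 clusters, 60 low-birth-weight babies each, 13% v 9%, alpha 0.05 (two-sided assumed), ICC 0.01 to 0.05. Design effect = 1 + 59 × ICC; effective n per arm = 45 × 60 / design effect. At ICC 0.03 the design effect is 2.77, n = 2700 / 2.77 = 975, and power is 80.6%. This reproduces the stated figure of slightly more than 80%. At ICC 0.01 power is 96.2%, and at 0.05 it is 65.7%. For a 25% reduction (13% to 9.75%), the hypothesis in Rationale for the trial, ICC 0.03 gives 61.8%. Power is not plentiful.

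**4. Simulated cost of permuting within country**

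Common assumptions: 102 clusters at the listed site sizes, control risk 13%, 30% of between-cluster variance lying between sites, two mortality levels. Clusters are randomised within strata. The block-adjusted difference in cluster rates is then tested by permuting either within country or within the strata. The correlation is between baseline and trial-period cluster mortality within site.

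- Set A: 30% effect, 60 babies per cluster, strata of site × earlier-trial arm × mortality half; 1000 trials, 299 permutations, error about 1 point.
- Set B: 25% effect, 49 babies per cluster (0.082 × 400 × 1.5 years = 49.2), strata of site × high/low mortality; 1000 trials, error about 1.5 points.

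Power, country v strata (gain in points):

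| Set | ICC | Correlation 0 | Correlation 0.5 | Correlation 0.8 |
|---|---|---|---|---|
| A | 0.03 | 90.4 v 90.3 (−0.1) | 90.3 v 91.8 (1.5) | 92.6 v 95.2 (2.6) |
| A | 0.05 | 79.8 v 80.9 (1.1) | 83.1 v 84.7 (1.6) | 85.5 v 90.6 (5.1) |
| B | 0.03 | 71 v 73 (2) | 73 v 79 (6) | 73 v 82 (9) |
| B | 0.05 | 62 v 62 (0) | 63 v 69 (6) | 63 v 76 (13) |

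Set A power exceeds the formula in step 3 because it uses 102 clusters and removes between-site variance.

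At ICC 0.01, a separate run of set B with 199 permutations gave 88 v 88 at correlation 0 and 89 v 90 at 0.5. In that run the limiting case of correlation 1 gave 88 v 93, 76 v 87 and 59 v 78 at ICC 0.01, 0.03 and 0.05.

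Null rejection at nominal 5% in set A, for correlations 0 / 0.5 / 0.8, with error about 0.6 points:

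- Country: 4.8 / 2.8 / 2.7% at ICC 0.03, and 3.7 / 4.0 / 1.6% at ICC 0.05.
- Strata: 5.3 / 3.0 / 5.5% and 4.6 / 4.5 / 3.8%.

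The strata test should be close to 5% by construction, so its spread shows the simulation noise. Country blocking never rejected more than 4.8%.

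**5. The Indian merger alone**

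In set A, permuting within site instead of country changed power by 0.3 points (92.6 to 92.9) to 2.0 points (79.8 to 81.8). Most of any larger loss comes from omitting the mortality stratum.

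**The case against.** The text does not say that country is the only blocking factor. Sites nest in countries, so a test that permutes within the full strata also blocks on country. On that reading the promise of a test suited to the stratified randomisation and the country sentence can both hold. The model may also adjust for imbalanced baseline variables, and further model details are deferred.

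Part of this stands. The documents do not establish that the test will permute within country alone; what they show is a conflict in the text. But the country sentence covers both analyses and gives matching the randomisation as its reason, and that reason is wrong as written. The blocking variable is stated, not deferred. The covariate rule is conditional on imbalance, so it does not secure the stratification factors.

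A reader might infer three stronger things. One is a false-positive problem, but every run points the other way. Another is a definite loss of, say, 5 points or more; that needs strata that predict trial mortality well, and the protocol gives no such correlation. The third is a known inflation of the model standard errors, but no GEE or mixed-model calculation was run, so no size can be given.

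**Conclusion.** The stated blocking variable does not match the stated randomisation, and the Data analysis section conflicts with itself on the permutation test. If country were used as the permutation block, the test would be conservative and its intervals too wide. The power loss would be about nil at a baseline-to-trial correlation of 0, roughly 1 to 6 points at 0.5, and about 3 to 13 points at 0.8. These figures assume an ICC of 0.03 to 0.05, a 25% to 30% effect, two mortality levels and 30% of between-cluster variance between sites. At ICC 0.01 the loss is smaller. Type I error is not inflated. This is a correction of consistency and efficiency, not a threat to validity, but it should be made before outcome data are seen so that the reference distribution is not chosen afterwards.

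**What to change.** Replace the country sentence with:

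> The permutation test will re-randomise clusters within the actual randomisation strata (GN site, earlier-trial arm, baseline neonatal mortality stratum), and the GEE and mixed models will include GN site, earlier-trial arm and baseline cluster mortality as pre-specified covariates.

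Control for country is kept, because sites nest in countries. The cost is wording and a few lines of code, with no new data. One practical point: with two mortality levels, 7 × 2 × 2 = 28 strata hold 102 clusters, about 3.6 each, and Argentina's 6 clusters fall into four strata. Some strata may hold a single cluster. These carry no information in the permutation test, and the plan should say how they are handled.

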#### *Other secondary outcome measures*

The trial will also examine a number of additional clinical and process measures as secondary outcomes. For each of these outcome measures, descriptive statistics will be computed as described in the introductory paragraphs above. Model-based analyses will then be used to examine the effects of the intervention on each of clinical and process measures. For the clinical measures, GEE models will be used to evaluate the effect of the intervention on marginal risk of the outcome, with results reported for both unadjusted analyses and analyses controlling for covariates that differ across clusters. Also, generalized linear mixed models will be used to examine the effect of the intervention on subject-level risks. Again, results will be reported for both unadjusted and adjusted models.

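### The protocol gives the formal test to a permutation test but also labels the GEE primary, and it picks model covariates by observed imbalance instead of fixing the randomisation factors and baseline mortality in advance

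*Protocol article*

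**What the plan says.** Data analysis describes the primary comparison as "controlling for country, using two complementary approaches". The first approach has the formal role: "First, a cluster-based permutation test that is appropriate for the stratified randomization process be used to develop a formal hypothesis test and interval estimates". The second is a check on it: "A model-based analysis will be used to assess whether the inferences generated by the permutation test are robust enough to control for potential confounders".

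Two paragraphs later the roles shift. The text attaches the word primary to the model-based analysis and says that GEE, "as implemented through the SAS procedure GENMOD will be used for the primary analysis". No sentence says which result decides if the two differ.

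The same paragraph fixes how covariates enter: "If baseline differences between the treatment arms are identified, the covariables representing the imbalanced variables will be used for adjusted analyses". It gives no list and no threshold, only two examples (the share of hospital births and the type of birth attendant). Under Other secondary outcome measures the idea returns as "analyses controlling for covariates that differ across clusters", reported next to unadjusted results.

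Under Randomization procedures, registry data "will be used as a baseline to select the clusters" and to balance underlying neonatal mortality across arms. The strata are network site, arm in an earlier network trial, and neonatal mortality rate. Data analysis names only country as the blocking or stratification variable for both methods.

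**The concern.** There are three linked weaknesses.

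- **Which result governs.** A confirmatory test and a robustness check are different roles. Here the GEE holds both. If the permutation test and the GEE fall on opposite sides of 0.05, the protocol gives no way to decide.
- **How covariates are chosen.** In a randomised comparison, baseline differences between arms arise by chance. Choosing covariates by those differences makes the adjusted model depend on the data. It can bring in variables unrelated to mortality and leave out prognostic ones that happen to balance.
- **What is left out.** A cluster's earlier neonatal mortality is a natural predictor of its later mortality, and it was known before allocation. Stratifying on it makes a marked imbalance in it unlikely, so an imbalance trigger will tend to exclude it from the model.

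At stake are the precision of the model-based result and the clarity of the trial's main conclusion.

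**Working it through.** **The plan's own figure.** The Power estimates section has 90 clusters of 60, 13% versus 9%, alpha 0.05 and power slightly above 80%. The ICC used is not stated; the protocol gives 0.01 to 0.05. I take 0.03 and a two-sided test.

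- Design effect = 1 + 59 × 0.03 = 2.77.
- Effective n per arm = 45 × 60 / 2.77 = 975.
- SE = √[(0.13 × 0.87 + 0.09 × 0.91) / 975] = 0.01414.
- Power = Φ(0.04 / 0.01414 − 1.96) = Φ(0.87) = 81%.

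The stated figure reproduces, so the same formula is used below.

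**Gain from a fixed baseline covariate.** Inputs from the protocol:

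- 102 clusters.
- 400 deliveries a year × 1.5 years × 8.2% = 49 small births per cluster.
- 13% control mortality and the hypothesised 25% reduction, giving 0.13 × 0.75 = 9.75%.

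Inputs assumed, because the protocol does not give them: 50 baseline small births per cluster, and a correlation s of 0.5 to 0.8 between a cluster's true rates in the two periods.

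- Reliability of a cluster rate from m births: m × ICC / (1 + (m − 1) × ICC).
- Variance explained: r² = s² × baseline reliability × trial reliability.
- Adjusted design effect: (1 + 48 × ICC) × (1 − r²).

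At ICC 0.03 the reliabilities are 0.607 and 0.602. So r² runs from 0.25 × 0.366 = 0.09 to 0.64 × 0.366 = 0.23. The design effect falls from 2.44 to between 2.22 and 1.87, and effective n per arm rises from 1,024 to between 1,127 and 1,337.

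| ICC | r² | Power, unadjusted | Power, baseline-adjusted |
|---|---|---|---|
| 0.01 | 0.03–0.07 | 85% | 86%–87% |
| 0.03 | 0.09–0.23 | 64% | 68%–76% |
| 0.05 | 0.13–0.33 | 50% | 56%–67% |

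These gains are before anything that stratified analysis or country control already recovers. With s as low as 0.3, the gain at ICC 0.03 is only from 64% to about 65.5%. In the protocol's own scenario (90 clusters of 60, 13% versus 9%, ICC 0.03), the same method with 30 to 60 baseline births takes power from 81% to 84%–91%.

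**Behaviour of the imbalance rule.** With 5 to 10 independent baseline variables each tested at 0.05 (an assumption, since no threshold is given), the chance of at least one flag is 1 − 0.95⁵ = 23% to 1 − 0.95¹⁰ = 40%. A simulation used 90 cluster means, five covariates of which one was prognostic (correlation 0.3 or 0.5 with the outcome), and 20,000 runs per setting:

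| Adjustment | Type I error | Power |
|---|---|---|
| None | 5.0% | 79.3%–79.6% |
| Chosen by imbalance | 4.4%–4.7% | 79.0%–80.3% |
| Prognostic covariate, fixed | 4.8%–5.1% | 82.7%–89.3% |

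Choosing by imbalance gained essentially nothing over no adjustment and did not inflate the error.

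**Two tests.** If success on either of two 0.05 tests were claimed, the bivariate normal error is 6.5% at a correlation of 0.95 and 5.7% at 0.99. A simulated unadjusted cluster-level test against an independence GEE (102 clusters of varying size, ICC 0.03) gave a correlation of about 0.95 and an either-or error of about 6.1%.

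**The case against.** The first paragraph of Data analysis does lean clearly to the permutation test: it alone is given the formal test and interval, and the approaches are called complementary. This stands. The fault is a later, conflicting label, not the lack of any formal test.

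A reader might infer that the imbalance rule undermines the trial's formal test. The text does not support that. The rule sits in the paragraph on the model and governs adjusted analyses; nothing applies it to the permutation test, and the simulation shows no inflation.

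A reader might also infer that baseline mortality is ignored unless it is imbalanced. That too goes beyond the text. The permutation test is to be "a cluster-based permutation test that is appropriate for the stratified randomization process", which naturally means permuting within the randomisation strata, so baseline mortality may already enter it coarsely. The sentence naming only country leaves this unclear.

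A reader might take the either-or figures as the trial's real error rate. The protocol nowhere states a rule of success on either method, so they are a hypothetical worst case.

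Finally, model details are deferred to a statistical analysis plan that is not shown. That covers further detail, but the selection rule and the conflicting labels are fixed in the protocol itself.

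**Conclusion.** The point holds as a modest fault of specification. On the text alone, three things are firm: the GEE is called primary after the formal test has been given to the permutation test, with no governing rule; covariates for the adjusted model are selected by observed imbalance; and only country is named in the analysis, although site, previous-trial arm and neonatal mortality rate defined the strata.

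The consequence is lost precision and data-dependent adjustment in the model results, and an avoidable dispute if the methods disagree. No material inflation of type I error has been shown. The size of the precision loss is uncertain: close to nil at an ICC of 0.01, and 4 to 12 percentage points of power at 0.03 under the assumed stability and baseline numbers, before any gain from strata or country.

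**What to change.** 1. Name one confirmatory analysis: the permutation test, with permutation within the actual randomisation strata. Call the GEE and the mixed model supportive, and remove the word primary from both mentions of the model.
2. Replace the imbalance rule, here and for the secondary outcomes, with covariates fixed in advance: the randomisation factors and cluster-level baseline neonatal mortality from the registry.
3. Define that baseline measure exactly (population, age at death, period). The randomisation section speaks only of the neonatal mortality rate, not of 28-day mortality in small babies.
4. Optionally use the same covariate in the permutation test, for example by permuting cluster rates residualised for baseline mortality. This is one valid choice among several.

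The cost is a few sentences in the protocol and the analysis plan, settled before outcomes by arm are seen. No new data are needed, because the registry already holds the baseline.
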